#### Illness Severity

Blood lactate levels will be measured before intervention and 30 minutes post intervention with arterial blood using a standard benchtop Arterial Blood Gas Analyser (ABL 700 Series gas Machines, RADIOMETER, Copenhagen, Denmark). Lactate concentration trends will be used to analyse lactate clearance rates [71] as a marker of illness severity.

#### Muscle oxygenation and Microcirculation

Muscle oxygenation and microcirculatory changes will be measured using the Near Infrared Oxygenation (NIR0) Monitor and the Orthogonal Polarization Spectral (OPS) Microscan respectively.

Muscle (tissue) oxygenation will be measured pre and post intervention daily using the NIRO (NIRO-200, Hamamatsu, Japan) with a probe placed on a peripheral muscle to detect levels of muscle oxygenation (StO_2_) following acute exercise [72]. Muscle oxygen consumption will be further analysed through induced ischemia and active hyperaemia [73]. A pneumatic cuff will be placed above the elbow and inflated to 50 mmHg above the patient's systolic blood pressure and the occlusion will be retained for 3 minutes inducing local ischemia. StO_2 _will be recorded continuously for 3 minutes before, during and after arterial occlusion [44].

Improvements in microcirculation following acute exercise will be measured pre and post intervention session once weekly using the OPS MicroScan (Microvision Medical Inc, Wallingford, PA, USA) with a non-invasive probe placed in the sub-lingual space to detect functional capillary density and blood flow velocity as indicators of microcirculatory function [74] using video images. Five video sequences per patient will be graded by 3 independent observers and assigned a flow velocity score to each of the 4 quadrants of each image [75]. Capillary density will be calculated using superimposed calibrated grid of vertical and horizontal lines on the images of number of small (< 20 μm) vessels crossing the lines of the grid divided by the total length of the lines, yielding the number of small vessels per millimetre [76]. An average of these 5 readings will be calculated for discrete capillary density value for each time point at which imaging was performed.

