### Hypotheses and Aims

The primary research hypothesis of the "i-PERFORM Trial" is that patients with defined sepsis syndromes [57] in the ICU who participate in an early targeted rehabilitation program will have improved physical function and an improved quality of life. The secondary hypotheses is that there will be systemic effects underlying primary improvements which will include; increased fat free mass; decreased pro-inflammatory and increased anti-inflammatory cytokines; increased peripheral blood mitochondrial DNA content and reduced blood lactate levels; and improved tissue oxygenation and microcirculation flow.

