### Sample size

Clinically important difference and the standard deviation estimates used in our sample size calculations were based on a previous clinical trial [64]. Sample size was calculated using the ACIF [62] for hypothesis testing with a type I error rate of 0.05 and 0.025 with Bonferroni adjustment and type II error rate of 0.20 (80% power). A minimum of 35 per group (70 total) is required to detect a minimum clinical difference (effect size) of 0.7 for physical functional outcomes which will yield clinically significant results for the main hypothesis achievable by intervention. Projection of the sample size after adjusting for attrition or withdrawal rates, participation refusals and possible death due to sepsis; based on admission and mortality rates in the RBWH ICU, 126 patients per group (252 in total) will be required.

A smaller number of patients will undergo mtDNA, tissue oxygenation and microcirculatory measurements as these will be tested as pilot investigations. To test these secondary hypotheses, a minimum of 58 per group is required to detect a minimum clinical difference of 0.8 for clinically significant changes in mitochondrial DNA [78], a minimum 91 per group is required to detect a clinical difference of 0.4 and 59 per group is required to detect a minimum clinical difference of 0.7 for clinically significant changes in tissue oxygenation [45] and microcirculation [46] respectively, all corrected for with Bonferroni adjustment of 0.025.

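### The microcirculation section names functional capillary density, but its density formula has no flow condition and so gives total small-vessel density (minor; density readout only)

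*Protocol article*

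**What the plan says.** In the Protocol article, under Muscle oxygenation and Microcirculation, a sublingual probe is used before and after a session once a week "to detect functional capillary density and blood flow velocity as indicators of microcirculatory function". Two indicators are therefore named.

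- **Flow.** Three observers grade five video sequences per patient, each sequence being "assigned a flow velocity score to each of the 4 quadrants of each image".
- **Density.** The formula is the "number of small (< 20 μm) vessels crossing the lines of the grid divided by the total length of the lines". Its result is expressed as small vessels per mm. The summary step reads: "An average of these 5 readings will be calculated for discrete capillary density value for each time point".

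Under Hypotheses and Aims, the secondary hypothesis includes "improved tissue oxygenation and microcirculation flow". Under Sample size, the mtDNA, tissue oxygenation and microcirculation measurements are described as pilot work in a subset of patients. For microcirculation that section states that "59 per group is required to detect a minimum clinical difference of 0.7", at an adjusted level of 0.025.

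**The concern.** The density indicator is introduced with the word *functional*, which in its plain sense here means vessels that are carrying blood. The formula has one selection criterion, diameter below 20 μm. It does not mention flow, and the word *functional* does not appear again when the value is calculated or averaged. This is more than an abbreviated description: grid, size cut-off, denominator, unit and averaging are all fixed, and the variable they define differs from the one named.

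The hypothesis concerns flow. If exercise restored flow in vessels that were already visible but stagnant, the density value as written would not move. If more stagnant vessels came into view, it could move in the opposite direction to perfused density. A reader who took the value for functional density would then misread it. The wording also leaves room for the observers to apply different counting rules.

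**Working it through.** The plan gives no figure for this point that could be reproduced. The check compares the definitions and then illustrates the consequence.

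**1. Named measure against formula**

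| Element | What the article gives | Depends on flow? |
|---|---|---|
| Named indicators | Functional capillary density; blood flow velocity | Yes, for both (taking *functional* as flow-carrying) |
| Density formula | Small-vessel crossings ÷ total line length | No |
| Unit | Small vessels per mm | No |
| Value per time point | Mean of five density readings | No |
| Flow score | One score per image quadrant | Yes, but not per vessel |

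No step uses the flow score to filter or weight the count. Because it is given per quadrant, it could not identify which crossing vessels are flowing.

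**2. Consequence in symbols.** Let N be the small vessels crossing the grid, L the total line length and p the share of those vessels with flow.

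- Written rule: D = N / L
- Perfused density: F = p × N / L = p × D

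If N and L are unchanged, D is unchanged whatever p does, while F changes in proportion to p.

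**3. Illustration.** All values are assumed; the article gives none.

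| Visible vessels/mm, before → after | Flowing share, before → after | Written rule | Perfused density |
|---|---|---|---|
| 12 → 12 | 60% → 80% | 12 → 12 (0%) | 7.2 → 9.6 (+33%) |
| 12 → 12 | 70% → 90% | 12 → 12 (0%) | 8.4 → 10.8 (+29%) |
| 12 → 12 | 80% → 90% | 12 → 12 (0%) | 9.6 → 10.8 (+12.5%) |

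A change in the opposite direction is also possible. If visible vessels go from 9 to 10/mm while flowing vessels go from 7 to 6/mm, the written rule gives 1/9 = +11% and perfused density gives −1/7 = −14%.

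**4. Can a power loss be derived?** No, for two reasons.

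- The Sample size section attaches 0.7 and 59 per group to microcirculation in general. It does not say whether they refer to density, flow velocity or something else.
- The inputs behind the 59 cannot be recovered from what is stated. Taking 0.7 as a standardised difference, two-sided 0.025, and the 80% power given for the main calculation: n = 2 × (2.2414 + 0.8416)² / 0.7² = 2 × 9.505 / 0.49 = 38.8, so 39 per group (41 with the t distribution). That mismatch is a separate matter and bears on this point only by ruling out a power calculation.

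**The case against.** The strongest reply is that the same section measures flow directly. Blood flow velocity is a named indicator in its own right, scored in every quadrant by three observers, and it is the readout closest to the stated hypothesis. A reader might infer from the density formula that the trial will miss a change in perfusion. The article does not support that: in each illustration above, the flow score could register the change. This part of the reply stands and limits the point to the density value.

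Second, the article does not define *functional*, does not say that stagnant vessels are counted, and cites published methods for the indicators, the flow scoring and the density calculation. Those sources are not at hand and may contain a flow criterion. One can also read the formula as geometry to be applied to the measure already named. This stands as a caution. It does not remove the point, because the article prints a specific rule; if the intended method does restrict the count to flowing vessels, the printed rule misstates it and the same edit is needed.

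Third, the calculated value is called only capillary density, so it cannot be asserted that the result will be published as functional density. That is correct. Equally, no other derivation is offered for the functional density that is named.

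**Conclusion.** The point holds for the density readout. As written, the calculation yields total small-vessel density, does not match the indicator it is meant to deliver, and does not respond to a change in the share of visible vessels that are flowing.

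This rests on two assumptions: that *functional* means flow-carrying, and that the formula is applied literally. The numerical examples show how the rule behaves; they are not estimates for this trial.

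The severity is minor. The outcome is secondary and pilot-level, it has a second readout that measures flow, and no primary outcome is touched. A reader might want to translate the mismatch into reduced power at 59 per group. The article does not tie that number or the 0.7 to density, so no such figure can be supported.

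**What to change.** Amend the density derivation to count small (<20 μm) vessels **with visible flow** that cross the grid lines, divide by total line length, and average over the five sequences of that time point. Report total small-vessel density and the proportion of vessels perfused alongside, so that a change in visible vessels can be told apart from a change in flow.

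If the count is to stay as it is, call the measure total small-vessel density where the indicators are introduced, and rest any claim about flow on the flow velocity score.

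The cost is small: a sentence of wording, the same videos and the same observers, and some extra reading time to mark each crossing vessel as flowing or not. The second option needs only the wording change.

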### Confounding Variables

Critical illness neuropathy and myopathy is a possible feature of critically ill patients. Formal tests to establish critical illness neuropathy or myopathy can be painful, invasive, time consuming and expensive [6]. Such formal diagnosis may not implicate any pertinent findings in this trial. Basic physiotherapy assessment muscle testing done as part of regular intervention assessment using the Medical Research Council or Manual Muscle Test will detect any possible development of weakness without requirements for formal diagnosis and is accepted as configuration of critical illness polyneuromyopathy [77].

### Sample size

Clinically important difference and the standard deviation estimates used in our sample size calculations were based on a previous clinical trial [64]. Sample size was calculated using the ACIF [62] for hypothesis testing with a type I error rate of 0.05 and 0.025 with Bonferroni adjustment and type II error rate of 0.20 (80% power). A minimum of 35 per group (70 total) is required to detect a minimum clinical difference (effect size) of 0.7 for physical functional outcomes which will yield clinically significant results for the main hypothesis achievable by intervention. Projection of the sample size after adjusting for attrition or withdrawal rates, participation refusals and possible death due to sepsis; based on admission and mortality rates in the RBWH ICU, 126 patients per group (252 in total) will be required.

A smaller number of patients will undergo mtDNA, tissue oxygenation and microcirculatory measurements as these will be tested as pilot investigations. To test these secondary hypotheses, a minimum of 58 per group is required to detect a minimum clinical difference of 0.8 for clinically significant changes in mitochondrial DNA [78], a minimum 91 per group is required to detect a clinical difference of 0.4 and 59 per group is required to detect a minimum clinical difference of 0.7 for clinically significant changes in tissue oxygenation [45] and microcirculation [46] respectively, all corrected for with Bonferroni adjustment of 0.025.

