### Data Management and Statistical Analysis

A baseline comparison using both student t-tests and chi-square for equal proportions of demographic data will be done between groups at enrolment. Data will be analyzed using SPSS Version 17.0. The distribution, range of scores and heterogeneity will be examined for participants in both groups. Mean changes scores, standard deviations and 95% confidence intervals will be calculated and specific analysis detailed under each outcome measure will be performed. Repeated measures, between/within analysis of variance (ANOVA) will be performed to investigate for the main effects of time and group. Post hoc analyses will then be performed to ascertain where the differences occur. A Bonferroni correction will be used as the post hoc measure as there are multiple outcome measures. Analysis will be by both intention-to-treat and per-protocol method. Any violations of the protocol will be noted. Statistical significance will be set at p < 0.05 and p < 0.025(two-tailed). All efforts will be taken to avoid missing data but if it occurs a carry forward imputation will be done and linear mixed modelling will be used for overall analysis. Reasons for loss of follow up will be recorded.

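### The single minimum of 35 per group gives 80% power at two-sided 0.05 but only about 74% at the two-tailed 0.025 that the plan also sets

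*Protocol article*

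**What the plan says.** The Sample size section of the protocol article bases the calculation on the ACIF and names two error rates together: "Sample size was calculated using the ACIF [62] for hypothesis testing with a type I error rate of 0.05 and 0.025 with Bonferroni adjustment". It pairs both with one power target, "type II error rate of 0.20 (80% power" in brackets. One number follows: "A minimum of 35 per group (70 total) is required to detect a minimum clinical difference (effect size) of 0.7". No standard deviation is printed; the section says only that "Clinically important difference and the standard deviation estimates used in our sample size calculations were based on a previous clinical trial". The 35 is then raised to 126 per group (252 in total) for attrition, refusals and deaths, without stated rates.

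The Data Management and Statistical Analysis section supplies the sidedness and keeps both thresholds: "Statistical significance will be set at p < 0.05 and p < 0.025(two-tailed". It calls for a Bonferroni correction because there are several outcome measures. Two physical function tests, the ACIF and the PFIT, are among the primary outcomes.

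**The concern.** With effect size and power fixed, a stricter error rate needs more patients, so one minimum cannot be the right answer at both 0.05 and 0.025. The text gives one figure and leaves the reader to take it as valid for either.

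The stricter level matters here. Halving 0.05 is the Bonferroni division for two tests, and physical function has two primary measures. If the main hypothesis is judged at 0.025, the power that counts is the power at 0.025. If 35 was derived at 0.05, that power is nowhere stated and is below 80%. The Discussion describes the trial as fully powered, so readers will rely on this figure.

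**Working it through.** **Inputs**
- Effect size d = 0.7 (Sample size section). The section itself calls it an effect size, so it is read as a difference in SD units, with SD = 1.
- Power 80% (Sample size section), so z = 0.8416.
- Type I error rate 0.05 or 0.025 (Sample size section), two-sided (Data Management and Statistical Analysis section), so z = 1.9600 or 2.2414.
- Equal groups (126 and 126).
- Assumption: a plain two-group comparison of means without baseline adjustment.

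**Formulas (normal approximation)**
- n per group = 2(z₁₋α/₂ + z₀.₈₀)² / d²
- Power ≈ Φ(d√(n/2) − z₁₋α/₂)

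The t-test values below come from the noncentral t distribution.

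**Step 1. Reproduce the plan's figure at two-sided 0.05**
- n = 2(1.9600 + 0.8416)² / 0.49 = 32.04, so 33 per group. The t-test gives 33.02, so 34.
- Power at 35: 0.7 × √17.5 = 2.928, and Φ(2.928 − 1.960) = 83.4%. The t-test gives 82.3%.
- The stated 35 is therefore reproduced to within one or two patients per group.

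**Step 2. The same calculation at two-sided 0.025**
- n = 2(2.2414 + 0.8416)² / 0.49 = 38.80, so 39 per group. The t-test gives 40.08, so 41.
- Power at 35: Φ(2.928 − 2.241) = 75.4%. The t-test gives 73.7%.
- Effect detectable with 80% power at 35 per group: 0.75 by t-test (0.74 by normal approximation).

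| Two-sided error rate | n per group for 80% power, normal / t | Power at 35, normal / t |
|---|---|---|
| 0.05 | 33 / 34 | 83.4% / 82.3% |
| 0.025 | 39 / 41 | 75.4% / 73.7% |

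The shortfall at 0.025 is 4 to 6 evaluable patients per group.

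**Step 3. Does it reach enrolment?**
- Going from 126 to 35 is a reduction of 1 − 35/126 = 72.2%.
- Going from 126 to 41 is a reduction of 1 − 41/126 = 67.5%.
- So 126 randomised per group still leave 41 evaluable at up to 67% loss. The stated allowance also counts refusals, which are not losses after randomisation.

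**Step 4. Other readings of 35**
- One-sided 0.025 is numerically the same as two-sided 0.05 and would reproduce 35, but the analysis section says two-tailed.
- One-sided 0.05 needs 26 per group, which does not match.

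**The case against.** **The text never attaches 35 to 0.025.** It lists two rates, then one number. The secondary sizes, by contrast, are expressly labelled "all corrected for with Bonferroni adjustment of 0.025", and the sentence with 35 has no such label. This stands. A reader might infer that the article claims 80% power with 35 per group at both levels, but the wording does not go that far. What remains is that the level behind 35 is unstated, and that the figure does not hold at the stricter of the two levels named beside it.

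**The planned analysis is more than a two-sample test.** Function is measured at baseline and ICU discharge, and repeated-measures ANOVA and mixed modelling are planned. If baseline adjustment is assumed, a baseline correlation of 0.3 gives 78.0% power at 35 per group and two-sided 0.025, and 0.4 gives 81.4%. So 74% belongs to the unadjusted comparison. The article states no correlation, however, and its own figure is reproduced without one.

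**Enrolment is unaffected.** This also stands. A reader might infer that 126 per group rests on a wrong base. The documents do not support that: no attrition, refusal or mortality rates are printed, so the step from 35 to 126 cannot be reconstructed.

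**The secondary sample sizes.** Setting 59 per group for 0.7 beside the primary 35 for 0.7 suggests a further error. That does not follow. Only the primary 0.7 is called an effect size; the others are clinical differences in different measurements from different sources and may be in raw units. Setting n = 2(2.2414 + 0.8416)² × SD² / difference², so that SD = difference × √(n/19.01), 58 for 0.8, 91 for 0.4 and 59 for 0.7 are all reproduced at two-sided 0.025 and 80% power, with SDs of about 1.4, 0.9 and 1.2. Nothing in the article rules these out.

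**Conclusion.** The point holds for the primary minimum. As written, 35 per group delivers the stated 80% power at two-sided 0.05 (82% by t-test) but not at the two-tailed 0.025 also named. There, power is about 74% (75% by normal approximation), and the minimum is short by 4 to 6 per group.

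This assumes that 0.7 is in SD units, which the article's own label and the match at 0.05 support, and that the comparison is unadjusted.

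The weight is moderate. The stated power is wrong at one of the two thresholds, but the trial would fall below 80% at 0.025 for this effect only if evaluable numbers dropped close to the bare minimum of 35.

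**What to change.** Correct one sentence in the Sample size section, in one of two ways:
- give the evaluable minimum as 41 per group (82 in total) at two-sided 0.025, or 39 per group (78 in total) if the normal approximation is used; or
- keep 35 per group, say that it applies to two-sided 0.05, and add that power at two-sided 0.025 is about 74%.

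Either way, name the error rate and its sidedness next to the number. The cost is the rewording alone: the planned 126 per group can stay.

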### Primary Outcome Measures

All primary outcomes will be measured at baseline (recruitment) and at ICU discharge and quality of life at 6 months post hospital discharge. The primary outcome measures will report the level of physical functioning and quality of life (long-term effects) of the participants. Physical function will be measured using the Acute Care Index of Function (ACIF) and the Physical Function ICU Test (PFIT).

The ACIF will essentially rate simple physical function (transfer bed to chair, sit to stand independently) of the patient on leaving the ICU [62]. The PFIT is a newly developed clinical tool for testing functional strength and endurance capacity in ICU patients. It consists of a battery of tests assessing endurance, muscle strength, cardiovascular capacity and functional ability which are domain representative of physical function and specific for the use of higher functional assessment in the critically ill [63]. These have been chosen as corresponding measuring instruments as they have demonstrated reliability, validity and responsiveness in the ICU population [63,64].

Quality of life will be measured using the Short Form-36 (SF-36) Health Survey Questionnaire. Information from the next of kin will be used to provide proxy scores which have been demonstrated to have good reliability and validity [65].

The constructs of psychological well being will be measured using the anxiety subscale of the Hospital Anxiety and Depression Scale (HADS) as psychological wellbeing is known to be highly correlated to functional physical outcomes [66].

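### The single primary sample size of 35 per group reaches the stated 80% power at two-sided 0.05 but gives only about 74% at the Bonferroni level of 0.025, where 41 per group are needed

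*Protocol article*

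**What the plan says.** The Sample size section calculates the primary sample size on the ACIF, with "type I error rate of 0.05 and 0.025 with Bonferroni adjustment" and "type II error rate of 0.20 (80% power". It then gives one minimum: "A minimum of 35 per group (70 total) is required to detect a minimum clinical difference (effect size) of 0.7". It does not say which of the two error rates that number belongs to. For the inputs it says: "Clinically important difference and the standard deviation estimates used in our sample size calculations were based on a previous clinical trial". No SD is printed and no test is named.

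The minimum is then projected to 126 per group (252 in total) for attrition or withdrawal, refusals and death. No loss rate is given.

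Data Management and Statistical Analysis adds: "Statistical significance will be set at p < 0.05 and p < 0.025(two-tailed". It also applies a Bonferroni correction because there are several outcome measures. Under Primary Outcome Measures, two instruments cover physical function: "Physical function will be measured using the Acute Care Index of Function (ACIF) and the Physical Function ICU Test (PFIT". Dividing 0.05 by these two gives 0.025. That link is my inference; the article does not state the divisor.

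**The concern.** Two significance levels cannot share one minimum sample size at the same effect and the same power. The stricter level needs more patients. If 35 belongs to 0.05, the statement is incomplete for 0.025. If it is meant to cover both, it is wrong for 0.025.

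This matters because it is the only power statement for the primary outcome, the figure of 126 per group is projected from it, and the Discussion describes the trial as fully powered. A reader who takes the sentence at face value will believe that the adjusted comparison carries a 20% type II error.

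**Working it through.** **Inputs**
- Effect size d = 0.7 (Sample size section, where it is labelled an effect size). I take it in SD units.
- Power 80% (same section).
- Alpha 0.05 and 0.025 (same section), both two-tailed (statistical analysis section).
- Equal allocation: 35 per group, 70 total.
- Assumed: an unadjusted two-sample comparison of means.

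**Normal approximation**

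n per group = 2 (z₁₋α/₂ + z₀.₈₀)² / d²

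- Alpha 0.05: 2 × (1.960 + 0.842)² / 0.49 = 32.04, so 33.
- Alpha 0.025: 2 × (2.241 + 0.842)² / 0.49 = 38.80, so 39.

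Power at n = 35 is Φ(d√(n/2) − z₁₋α/₂), with d√(n/2) = 0.7 × √17.5 = 2.928.

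- Alpha 0.05: Φ(2.928 − 1.960) = 83.4%.
- Alpha 0.025: Φ(2.928 − 2.241) = 75.4%.

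**Two-sample t-test (noncentral t)**

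| Two-sided alpha | n per group for 80% power | Power at 35 per group | Effect detectable at 35 with 80% power |
|---|---|---|---|
| 0.05 | 33.02, so 34 | 82.3% | 0.68 SD |
| 0.025 | 40.08, so 41 | 73.7% | 0.75 SD |

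At 0.025, 40 per group give 79.9% and 41 give 81.0%.

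**Reproducing the printed figure.** The 35 is within one or two patients of the result at two-sided 0.05 (34 by t-test, 33 by normal approximation). At two-sided 0.025 it falls short by 6 (t-test) or 4 (normal approximation), so neither rounding nor the choice of formula explains the gap. One-sided 0.025 would also give 34, but the analysis section says two-tailed.

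**Effect on enrolment**
- Implied by the article: 35/126 = 27.8% evaluable, so 72% loss tolerated.
- With 41: 41/126 = 32.5% evaluable, so about 67% loss tolerated.
- Keeping the article's own ratio (126/35 = 3.6) would give 41 × 3.6 = 147.6, so 148 per group.
- With all 126 per group evaluable, power at 0.025 exceeds 99%.

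**The case against.** **The 35 is right at one of the stated levels.** This stands. The secondary sample sizes are expressly labelled as corrected to 0.025 and the 35 is not, so one can read 0.05 as the level for the main calculation. But the sentence naming both rates is the one about the ACIF, so the text does not settle it. On either reading the article gives no correct figure for the primary outcome at 0.025.

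**The test and the SD are unknown.** This also stands as a limit. Baseline and discharge are both measured, and repeated-measures ANOVA and mixed modelling are planned. If 0.7 refers to the SD of the raw score and the analysis adjusts for baseline with correlation r, then n × (1 − r²) applies: 40.08 × (1 − r²) = 35 gives r of about 0.36. The article states no correlation and no such adjustment in the calculation. If 0.7 were in raw units, 35 per group at 0.025 would need an SD of about 0.93. Against that, the effect size label and the near match at 0.05 favour the standardised, unadjusted reading.

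**Enrolment of 126 per group absorbs the gap.** Largely true. A 45% loss, borrowing the septic shock mortality in Table 1, leaves about 69 per group (0.55 × 126 = 69.3) and 96.7% power at 0.025. A 60% loss leaves about 50 and roughly 89%. Power drops below 80% only if about two thirds or more are lost. Yet the article's own projection from 35 to 126 allows for a 72% reduction, and there about 35 remain, with power near 74%.

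**A tempting extra argument.** A reader might cite the secondary microcirculation figure as proof that the primary one is too small: "59 per group is required to detect a minimum clinical difference of 0.7", also at 0.025. The article does not support this. That 0.7 concerns another outcome, comes from another source and is not labelled an effect size. In SD units at 0.025 it would need 41, not 59, so it does not corroborate 41.

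**Conclusion.** The point holds in a limited form. The 35 per group is consistent with 80% power at two-sided 0.05 and not at two-sided 0.025, although the sentence names both levels. At 0.025, power is about 74%, so the type II error is about 26% instead of 20%.

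This rests on 0.7 being a standardised difference and on an unadjusted two-sample t-test. The normal approximation leads to the same conclusion.

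A reader might infer that the trial is underpowered or must recruit more patients. The article does not show that: it gives no loss rate, and 126 per group keeps at least 80% power at 0.025 unless about two thirds or more are lost. What needs correcting is a stated figure that the plan relies on, and the correction is of moderate importance.

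**What to change.** Restate the primary calculation in the Sample size section with each number tied to its alpha, in one of two ways:

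- 41 evaluable per group (82 total) for an effect size of 0.7, 80% power, two-sided 0.025; or
- 35 per group (70 total), with 82% power at two-sided 0.05 and about 74% at two-sided 0.025 (detectable effect 0.75 SD).

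In the same place, name the test and give the SD behind the 0.7. If a baseline adjustment was used, state the assumed correlation.

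Enrolment of 126 per group can stay. The text should then say that 80% power at 0.025 tolerates about 67% loss instead of the 72% implied by 35 of 126.

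The cost is a sentence or two of text and, under the second option, a less favourable power figure. No extra patients are needed, and conduct and analysis do not change.
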